### Participant eligibility criteria

Patients eligible for this analysis must (1) be aged 18 years or older, (2) be overweight (BMI ≥25 kg/m^2^) at initial visit, and (3) have had at least one weight-prioritized visit in a participating clinic. Exclusion criteria in the original protocol include limited cognitive ability, have a non-home residence, or have less than 1-year life expectancy. Ultimately, these were not applied due to the inability to obtain the necessary fields in the data extraction; however, the number of individuals that would be excluded based on these criteria is expected to be minimal and balanced across the study arms. Weight-prioritized visits are defined as the chief complaint or reason for the visit being at least one of the following: (1) “overweight,” “obesity,” or “weight,” (2) ICD-10-CM codes for billing E66–E.66.9, Z68.25–45, (3) use of the “obesity brief HPI” Epic flowsheet, or (4) the PATHWEIGH patient questionnaire.

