### Interventions

#### Current standard of care (SOC)

SOC will be the control condition that patients will receive during the control phases of the design. Clinics in the SOC condition will conduct visits in which weight may be discussed (defined as “weight-prioritized” for purposes of data extraction) without access to either the PATHWEIGH tools in Epic or the PATHWEIGH implementation strategies. Current SOC for obesity in the primary care clinics is called “obesity – brief history of present illness (HPI),” and the option to select “Obesity brief HPI” is currently available to all Epic users at all practices. For an example of the Obesity brief HPI questionnaires, see Additional File Fig. S1. For a weight prioritized visit, this entails a brief historical intake of a patient’s weight and is intended to initiate a discussion regarding potential strategies for weight loss. Because SOC can be highly variable, we will conduct fidelity checks by performing sensitivity analyses for the use of the “Obesity brief HPI” in the SOC clinics at our every 6-month data extractions. A change in the use of the “Obesity brief HPI” by more than 30% between 6-month intervals will be investigated. There are currently no systematic weight management interventions at the clinics.

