#### Clinician workflow

To optimize efficiency and guide care, health care providers are encouraged to use the PATHWEIGH weight management SmartSet in Epic. A SmartSet is a documentation template used in the ambulatory setting comprised of a group of orders and other elements, such as notes, chief complaints, medications, and levels of service charges, that are commonly used together to document a specific type of visit. This SmartSet addresses the following.
Diagnosing overweight or obese patients with a BMI > 25 kg/m^2^ or > 30 kg/m^2^, respectively, recognizing these as bona fide disease states [6]Linking diagnoses for weight-related comorbidities to facilitate reimbursementPre-populating information from the patient weight management questionnaire to serve as documentation and to guide the clinician-patient discussion, and flagging weight management strategies based on guidelines from the Obesity Society [32], specifically, the discussion of lifestyle change for patients with BMI ≥ 25 kg/m^2^, consideration of medications impacting obesity as well as anti-obesity medication at BMI ≥ 30 kg/m^2^ (or BMI ≥ 27 kg/m^2^ with weight-related comorbidities) and consideration of bariatric surgery for BMI ≥ 40 kg/m^2^ (or BMI ≥35 kg/m^2^ with weight-related comorbidities)Providing options for orders that include laboratory testing, referrals, or procedures

Behavioral health professionals work alongside many of the primary care providers and are encouraged adjuncts to facilitate weight loss. Use of the PATHWEIGH tools is entirely optional for clinicians. Use may be deployed by the clinicians in advance of the visit or if they or the patient spontaneously decides to prioritize weight management. The process strongly encourages regular follow-up (usually at 4–6 week intervals and more often initially). A key advantage is that the clinician is the patient’s regular provider and will have an ongoing relationship with the patient over time and can safely manage or discontinue medications or other issues for weight-related comorbidities.

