The primary analysis is expected to provide a conservative estimate of the treatment effect, and we propose the following secondary analyses to assess the treatment effect in alternative cohorts. We will perform a per-protocol analysis that uses the described models to compare those that received PATHWEIGH to those with a SOC weight-prioritized visit. This analysis will provide a better estimate of the efficacy of the intervention by including only those in the PATHWEIGH condition that were considered to satisfy the criteria for receiving the intervention as assessed by the provider’s use of at least one of a weight prioritized visit “type”, the patient weight management questionnaire, and/or the weight management SmartSet. Additionally, we will perform an analysis using all those that are eligible for PATHWEIGH based on the criteria of age and BMI, regardless of whether they had a weight-prioritized visit. This analysis will allow us to account for the potential selection bias induced by the implementation of PATHWEIGH potentially increasing the number of weight-prioritized visits and thus increasing the enrollment of patients in the intervention period that differ systematically from those in the control period.

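### The per-protocol analysis filters only the PATHWEIGH side on optional tool use, so calling it a better estimate of efficacy is unjustified as written

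*Protocol article*

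**What the plan says.** All references are to the protocol article.

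- **The comparison.** Under Aim 1, Analysis, the per-protocol analysis will "compare those that received PATHWEIGH to those with a SOC weight-prioritized visit". On the PATHWEIGH side it keeps only patients "that were considered to satisfy the criteria for receiving the intervention as assessed by" the provider's use of at least one of three things: the weight-prioritized visit type, the patient questionnaire or the SmartSet. No restriction is stated for SOC.
- **The interpretation.** "This analysis will provide a better estimate of the efficacy of the intervention by including only those in the PATHWEIGH condition" who meet that criterion. The same paragraph describes the primary analysis as likely to be conservative.
- **The model.** "We will perform a per-protocol analysis that uses the described models", that is, the Aim 1 mixed models. These have random intercepts for provider and clinic, and covariates that enter if univariate models flag them as potential confounders.
- **Who uses the tools.** Clinician workflow: "Use of the PATHWEIGH tools is entirely optional for clinicians", and "Use may be deployed by the clinicians in advance of the visit or if they or the patient spontaneously decides to prioritize weight management". Under Staff workflow, patients who want help with their weight book the visit type, and that booking triggers the questionnaire.
- **Who enters the cohort.** Under Participant eligibility criteria, one of the four routes to a weight-prioritized visit is a billing code alone: "ICD-10-CM codes for billing E66–E.66.9, Z68.25–45".
- **Selection bias.** The article raises it only for the extra weight-prioritized visits that PATHWEIGH may generate, and answers it with the analysis of all patients eligible by age and BMI.

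**The concern.** The randomized schedule decides when a clinic changes condition. It does not decide which patients or clinicians then use the tools. Keeping users only, on one side only, compares a self-selected part of the PATHWEIGH condition with the whole SOC cohort. That cohort includes patients who would not have used the tools had they been available, and patients who qualified by code alone. If the two kinds of patient would lose different amounts of weight without any intervention, the contrast shows a difference even when PATHWEIGH does nothing.

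What is at stake is interpretation. The article presents the primary estimate as conservative and this one as better. On that wording, a positive per-protocol result beside a null primary result could be taken as evidence of efficacy, although selection might explain all of it. The all-eligible analysis does not help here, because it addresses who gets a weight-prioritized visit and not who is retained by the tool-use filter.

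**Working it through.** **1. Reproducing the plan's own figures.** Inputs from Sample size, Design and randomization, and Table 1: 4 one-year periods; sequences of 20, 18 and 19 clinics; 30 patients per clinic per year; ICC 0.02 to 0.05; two-sided alpha 0.05; 80% power; SD 10.7 kg. Using the Hussey–Hughes generalized least squares variance on clinic-period means, the detectable standardized effect is (1.960 + 0.842) × SE. This gives 0.1170 (ICC 0.02) and 0.1201 (ICC 0.05), against the stated 0.118 and 0.121. In kilograms, 0.118 × 10.7 = 1.26 and 0.121 × 10.7 = 1.29, as stated. The variance model is therefore a fair base for the illustration. The article gives no figure for the per-protocol analysis itself.

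**2. The bias under no true effect.** Let u be the share of PATHWEIGH-condition patients counted as users. Let D be the difference in mean 6-month weight loss between user-type and non-user-type patients that exists without any treatment effect. Both are assumptions. Suppose the mix of types is the same in the two conditions and there is no covariate adjustment.

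- SOC mean = u × (user mean) + (1 − u) × (non-user mean)
- Filtered PATHWEIGH mean = user mean
- Difference = (1 − u) × D

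**3. Numbers.** The last column is the chance of a two-sided p < 0.05 at ICC 0.05, from the same variance with 30 × u patients per clinic in intervention periods.

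| u | Bias, D = 1 kg | Bias, D = 2 kg | Bias, D = 3 kg | p < 0.05 for D = 1, 2, 3 kg |
|---|---|---|---|---|
| 30% | 0.7 | 1.4 | 2.1 | 20%, 61%, 92% |
| 50% | 0.5 | 1.0 | 1.5 | 15%, 45%, 79% |
| 70% | 0.3 | 0.6 | 0.9 | 9%, 23%, 44% |
| 90% | 0.1 | 0.2 | 0.3 | not computed |

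Simulation at ICC 0.05 (500 trials per scenario) with D = 2 kg gave 64%, 45% and 25% at u = 30%, 50% and 70%. The unfiltered comparison stayed at 4% to 5%. With D = 0 and u = 50% the filtered comparison rejected in 5.4%. So it is the selection that creates the false positives, not the smaller sample.

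**4. The right yardstick.** The stated 1.26 to 1.29 kg applies to the full sample. Filtering raises the SE. At u = 50% it is 0.528 kg (ICC 0.02) to 0.543 kg (ICC 0.05), so the detectable difference is 2.802 × 0.528 = 1.48 kg to 2.802 × 0.543 = 1.52 kg. At u = 30% the SEs of 0.611 and 0.625 kg give 1.71 to 1.75 kg.

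**5. Simplification.** The check uses one weight change per patient, a clinic random effect and fixed period effects. It omits the article's repeated weights, provider intercepts and screened covariates. It shows what unadjusted selection can do and does not predict the trial's result.

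**The case against.** Four points on the other side deserve weight.

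- **Some adjustment is provided.** A reader might infer that the model has nothing to make the groups comparable. That is not so. Patient-, provider- and practice-level covariates can enter, the Outcomes and Measures section lists the data to be collected on potential confounders, and provider and clinic have random intercepts. This stands. It may remove part of the bias, but nothing in the article shows that univariate screening of these fields captures motivation or engagement.
- **Direction is not established.** A reader might infer that the analysis is biased toward PATHWEIGH. The article reports no relation between tool use and prognosis. Motivated patients booking the visit would push the contrast that way, while clinicians keeping the tools for harder cases would push it the other way. This stands.
- **Size is not established.** A reader might set an assumed bias against the 1.26 to 1.29 kg detectable difference and conclude that selection alone reaches it. That benchmark belongs to the full sample, and both u and D are assumed. Table 3 tracks clinician use in more than half of weight-prioritized visits as a fidelity measure. That makes partial use a reasonable scenario but is not a forecast. If nearly everyone is a user, the bias is small.
- **It is a secondary analysis.** The primary analysis follows clinic condition at the index visit and does not apply this filter. This stands, and it limits the severity. It does not rescue the flat statement about efficacy.

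**Conclusion.** The point holds as a fault of interpretation in a secondary analysis. The per-protocol contrast conditions on optional behaviour after assignment, in one condition only, so it is not protected by the randomization. The claim that it better estimates efficacy is unjustified as written. This does not show that the estimate will be wrong, nor in which direction, and it leaves the primary analysis untouched.

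Over D = 1 to 3 kg and u = 30% to 70%, selection alone gives a spurious difference of 0.3 to 2.1 kg. The chance of nominal significance is about 9% to 93% across ICC 0.02 to 0.05. At u = 90% and D = 2 kg the difference is 0.2 kg. These figures assume no true effect, no covariate adjustment and the same patient mix in both conditions. The article supplies neither u nor D, so no corrected estimate can be given.

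**What to change.** 1. **Replace the efficacy sentence.** State that this is an as-treated, associational comparison, open to selection bias, and that it cannot support an efficacy claim when the primary analysis is null.
2. **Add a sensitivity analysis.** Weight or match SOC patients on pre-index predictors of tool use: baseline BMI, comorbidity, prior weight visits and provider characteristics. The tools do not exist in SOC, so the model for tool use has to be fitted in the intervention condition and applied to SOC patients. State that unmeasured motivation remains.
3. **Do not repair it by dropping code-only visits.** SmartSet use counts as receipt of PATHWEIGH but is not a route into the cohort, and Table 2 says that the Epic tool adds the overweight or obesity diagnosis automatically. A SmartSet-only recipient may therefore enter by code, and would be lost from the PATHWEIGH side. Restricting SOC to users of the Obesity brief HPI is at best a rough match. That form "is currently available to all Epic users at all practices", but selecting it is itself a choice, and it does not identify patients who would have used PATHWEIGH.

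The cost is a change of wording, a little extra analysis and a less favourable label on a secondary result.

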### Aim 2: Identify patient, provider, and clinic-level predictors that are associated with weight loss and weight loss maintenance

#### Outcomes and measures

Patient-level predictors will be captured from the EMR for each visit. Potential patient-level moderators will include age, sex, race/ethnicity, insurance status, baseline BMI, baseline use of medication that may contribute to weight gain, and score > 9 on Patient Health Questionnaire-8 or -9 (PHQ8, PHQ9), or Generalized Anxiety Disorder-7 (GAD7). Patient-level mediators will include treatment prescribed, in particular prescription of anti-obesity medication and performance of an endoscopic or surgical procedure with bariatrics. Provider-level predictors that can be obtained from EMR include provider age, sex, years in practice, and percent time performing clinical duties. Practice-level predictors include patient and provider number and demographics for each, as well as payor mix.

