### Sample size

A conservative sample size estimate is 6840 total patients (120 patients per clinic from 57 clinics) that assume a minimum of 30 eligible patients per clinic per year based on the smallest clinic. We present the power calculations assuming an intraclass correlation coefficient (ICC) between 0.02 and 0.05. With this design, we will have 80% power (alpha=0.05, two-sided) to detect a standardized effect size of 0.118 (ICC=0.02) to 0.121 (ICC=0.05). For our primary effectiveness outcomes, we estimate a standard deviation (SD) of 10.1 percentage points for percentage change in weight using our pilot study, and a similar SD estimate of 10.7 for absolute (kg) change in weight. Thus, with 80% power we can detect a mean difference in weight change of 1.19 (ICC=0.02) to 1.22 (ICC=0.05) percentage points between the control and intervention conditions, and a mean difference in absolute weight change of 1.26 kg (ICC=0.02) to 1.29 kg (ICC=0.05).

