#### Analysis

Moderation will be evaluated by including an interaction term between the treatment variable and possible moderating variables in the outcome mixed effects regression models used in Aim 1. A significant interaction effect will conclude that the considered variable moderates the effect of PATHWEIGH on the outcome. Mediation analysis will be conducted using the multi-level modeling framework to account for clustering within clinics and providers [45, 46]. Clinic- and provider-level mediators will be restricted to those that can be collected from EMR in both the control and intervention phases. Specifically, we will fit two models: (1) a mediator model to describe the effect of the treatment on the mediator, and (2) an outcomes model to describe the effect of the mediator on the outcome, adjusting for the treatment. Additionally, to be considered a mediator, change in the mediator variable must occur prior to or during the period of patient-level change. Both models will be adjusted for relevant patient-, provider-, and clinic-level variables. The outcomes model will additionally adjust for a time effect to account for temporal effects in the stepped wedge design. These models will be adjusted to include the appropriate random effects and variables based on the level of the considered mediator variable (i.e., patient, provider, clinic). The mediation effect will be summarized as the product of the treatment coefficient from the mediator model and the mediator coefficient from the outcomes model. We will test the null hypothesis that this product is equal to zero, and a statistically significant result will indicate that there is strong evidence that the effect of the treatment on the outcome is mediated by the considered variable. If necessary, we will explore more complex multi-level structural equation models [47].

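### Depression and anxiety moderators are specified only as a yes/no cut at 9, which would cost the interaction test a substantial share of its information if moderation is roughly linear, and the text leaves open whether they form one flag or two

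*Protocol article*

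**What the plan says.** The protocol article, Evaluation, Aim 2, Outcomes and measures, gives the moderators in one sentence. It opens "Potential patient-level moderators will include age, sex, race/ethnicity, insurance status, baseline BMI, baseline use of medication that may contribute to weight gain" and ends with the symptom measures, a "score > 9 on Patient Health Questionnaire-8 or -9 (PHQ8, PHQ9), or Generalized Anxiety Disorder-7 (GAD7"). Age and baseline BMI are named without a cut. The symptom scores are named only with one, and no reason for it is given.

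The Analysis subsection of Aim 2 states the test: "Moderation will be evaluated by including an interaction term between the treatment variable and possible moderating variables", added to the Aim 1 mixed models. It also states the rule for the conclusion: "A significant interaction effect will conclude that the considered variable moderates the effect of PATHWEIGH on the outcome".

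The only power statement in the article, under Sample size, concerns the overall intervention effect: "80% power (alpha=0.05, two-sided) to detect a standardized effect size of 0.118 (ICC=0.02) to 0.121 (ICC=0.05"). There is none for moderation. The article gives no distribution of PHQ or GAD7 scores and no share of patients above 9.

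**The concern.** Two things are at issue.

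- **The cut.** With a cut at 9, a patient who scores 9 is coded like one who scores 0, and all patients above 9 are coded alike. If the benefit of PATHWEIGH rises or falls steadily with symptom severity, the flag is a blunt proxy for the score. Interaction tests usually have less power than the test of the main effect, and the cut lowers it further. The plan then reads moderation off the significance of that interaction.
- **The wording.** Depression and anxiety share one list item, one threshold and the word 'or'. The sentence can mean one flag that is positive if either scale exceeds 9, or an indicator for each scale. Under the first meaning, a significant interaction would not show which of the two carries it.

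At stake is one of the moderator results for Aim 2 and Hypothesis II.

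**Working it through.** **1. The plan's own power figure.** Inputs from Sample size, Design and randomization, and Table 1: 57 clinics, three sequences, four one-year periods, 30 patients per clinic and year, two-sided alpha 0.05, 80% power. The Hussey-Hughes variance for a cross-sectional stepped wedge, in units of the total SD, is

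Var = I·s²(s² + T·τ²) / [(I·U − W)s² + (U² + I·T·U − T·W − I·V)τ²],

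with s² = (1 − ICC)/30 and τ² = ICC. I is the number of clinics and T the number of periods. U is the number of clinic-periods under intervention. W and V are the sums of squared intervention counts by period and by clinic.

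With 19 clinics per sequence, U = 114, W = 5054 and V = 266. At ICC 0.02:

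- s² = 0.03267
- Var = 0.2098/(1444 × 0.03267 + 3610 × 0.02) = 0.2098/119.37 = 0.001757, so SE = 0.0419
- detectable effect = 2.80 × 0.0419 = 0.117

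At ICC 0.05 the result is 0.120. With the actual 20/18/19 split the values are 0.1170 and 0.1201, and power at the stated effects is about 80.4% to 80.7% across the two layouts. The stated 0.118 and 0.121 therefore reproduce. So do 0.118 × 10.1 = 1.19 and 0.121 × 10.1 = 1.22 percentage points, 0.118 × 10.7 = 1.26 and 0.121 × 10.7 = 1.29 kg, and 120 × 57 = 6840. All of this concerns the main effect only.

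**2. Information kept by the cut, normal score.** Assume that moderation is linear in the score, and that the score varies among patients independently of condition. The information kept is then the squared correlation between flag and score. For a normal score with a share p above the cut, RE = φ(z_p)²/[p(1 − p)].

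If the numeric score has 80% power, the power of the flag is Φ(2.80·√RE − 1.96), where 2.80 = 1.96 + 0.84. The share p is an assumption throughout.

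| Share above 9 | RE | Information lost | Power of the flag |
|---|---|---|---|
| 50% | 0.637 | 36% | 61% |
| 30% | 0.576 | 42% | 57% |
| 20% | 0.490 | 51% | 50% |
| 10% | 0.342 | 66% | 37% |
| 5% | 0.224 | 78% | 26% |

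For example, at p = 0.30, φ(0.524) = 0.348 and 0.348²/0.21 = 0.576; then 2.80 × 0.759 − 1.96 = 0.165 and Φ(0.165) = 0.57.

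**3. Right-skewed integer scores.** Truncated negative-binomial scores on 0–27 (PHQ9) and 0–21 (GAD7) were used, with assumed means of 3 to 8 and dispersion parameters of 0.8 to 3. The loss runs from about 28% to 77%. Where 18% to 32% score above 9, it is about 28% to 39%. At a 28% loss, RE = 0.72 and 2.80 × 0.849 − 1.96 = 0.416, so the power is 66%.

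Across steps 2 and 3 the loss is about 28% to 78%, and the power about 66% down to 26%.

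**4. If one either-scale flag is meant.** Two normal scores were simulated with an assumed correlation of 0.5 to 0.8 and 10% to 30% above each cut. The flag loses about 47% to 71% of the information relative to the depression score alone.

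**5. If moderation is a threshold at the cut.** The flag then carries the whole effect and loses nothing.

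**The case against.** The best defence has four parts.

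- **Limited reach.** These are potential moderators in a secondary aim, and a journal article may leave coding detail to a fuller document. That limits the weight of the point. It does not remove it, because the cut is stated and other numeric moderators in the same sentence carry none.
- **The cut has a use.** A common threshold pools PHQ8 and PHQ9 totals without item-level data. That is a fair reason to report the flag. It is not a reason to test only the flag.
- **The sample may be much larger.** The article calls 6840 patients conservative. The share of information lost does not change with sample size, but the power cost shrinks when the starting power is well above 80%. The article gives no interaction power, so this stays open.
- **The decision rule is one-sided.** It says what a significant interaction shows. It does not say that a non-significant one rules moderation out.

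A reader might also infer more than the text supports:

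- **A fixed loss of about 40% to 65%.** This needs a normal score and some 10% to 35% of patients above the cut. Skewed scores can fall below that range.
- **That depression and anxiety are merged.** The sentence allows that reading but does not establish it.
- **That three scores are cut.** PHQ8 and PHQ9 are given as alternative versions, so there are two constructs.
- **That a real gradient would probably be missed.** With 20% to 30% above the cut, a normal score and 80% starting power, it would be found about 50% to 57% of the time.

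**Conclusion.** The point holds in conditional form. The article fixes the symptom moderators as a cut at 9, with no numeric version and no rationale, and does not settle whether they are one flag or two. The loss of about 28% to 78%, and the fall from 80% to between 66% and 26% power, rest on roughly linear moderation, on assumed score distributions and on assumed shares above 9. The power figures also assume 80% power for the numeric score. That a combined result could not be attributed to one construct depends on the either-scale reading. The primary analysis and the sample size are unaffected. This is a cheap improvement, not a flaw in the trial's main conclusion.

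**What to change.** In Aim 2, Outcomes and measures, replace the cut with two separate continuous moderators, the baseline PHQ total and the baseline GAD7 total. Fit each as a linear interaction and check it with a spline. Show results for scores of 9 or less and above 9 for display only. The word baseline is worth adding, because the sentence attaches it to BMI and medication use but not to these scores.

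Put PHQ8 and PHQ9 on a common scale by dropping the ninth item where item-level data are extracted. The article does not say that they are. Otherwise use the total with an indicator for the version.

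The cost is a short change to the analysis text and a little extra work to handle the two versions, provided that the totals are available from the data extraction. The downside is that a linear term assumes a gradient; the spline is there to check it.
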